### **Biofeedback Intervention Protocol**

The biofeedback intervention will be directed by [name], a clinical neuropsychologist at the Medical University of South Carolina (he will be hired as a consultant), and [name], who is trained in biofeedback therapy. A local biofeedback trainer with significant experience and certification will be hired for the intervention. Additionally, an experienced off-site HRVB trainer will be contracted to provide phone training for ½ of the sessions. HRVB training is conducted in an interactive manner using a computerized system to monitor and display the individuals' HRV patterns in real time while their heart rate is recorded. Visual HRV feedback (either a quantitative display or animated challenge games) is provided as participants practice attention focusing, resonant frequency breathing, imagery, and the induction of positive emotion. The resulting changes in HRV patterns are readily observed by the subject. The visual feedback enables associations to be formed between these techniques and HRV patterns indicative of higher vagal parasympathetic output. Before HRVB training, the biofeedback trainer discusses individual issues and the training goals of the participant. The physiological connection between resonant frequency breathing and heart rate is introduced. This is reinforced with corrective breathing instruction and help finding the resonant frequency (~6 respirations/min). Dual monitors also display the HRV power spectrum in real-time so that the participant can visualize

the impact of proper breathing on the coherence peak at 0.10 Hz. Positive emotion and interactive visual images are then introduced. This interactive process allows the participant to customize a sustainable system, with occasional shifts back to the power spectrum screen to observe the 0.10 Hz HRV peak. During the recording period after coaching, subjects view a static nature scene on the computer while their heart rate is measured by ECG.

### **Adherence Assessment**

The biofeedback coach will instruct participants in both groups to practice their training at home a minimum of 10 minutes a day, and a goal of 20 minutes per day. Participants will be given a log to record their daily home practice. Home practice self-report data will be incorporated into the analysis to examine the potential dose-response effects of home practice. Information will be solicited in a questionnaire at the start of each lab regarding the factors that contributed to or detracted from home practice, for inclusion in the analysis. One goal of this intervention is to spontaneously and consistently achieve HRV coherence on demand outside a clinical environment. Therefore, participants will be provided with a portable colorimetric finger PPG hand held personal stress reliever; dimensions similar to a cell phone; weight: 2.2 ounces for home practice and use between weekly HRVB training sessions. Home HRVB practice period data from the device can be compared to self-report and further analyzed with regard to the outcomes.

Personal HRVB coaching will be provided by HRVB trainer/mentors. These individuals are trained to teach the practical application of HRVB. Three individual mentoring sessions per participant will be provided via telephone or online via Skype to supplement acquisition of core HRVB skills through home practice. Through this program, the methods of achieving and sustaining HRV coherence are reinforced.

### **PET Imaging Protocol**

All studies will be acquired using a Siemens Biograph-40 3D PET/CT scanner (Knoxville, TN) comprised of a lutetium oxyorthosilicate (LSO) block detector ring of 162 mm field-of-view operating in 3D mode.

Images are acquired as follows: a scout is done to define scan range. A CT attenuation scan is performed with the lowest pitch allowed by the scanner, covering the region of interest in 14 seconds during shallow breathing. Two rubidium infusions of 1295 – 2220 MBq (35-60 mCi) are performed. A 7.5-minute rest emission scan in list mode is started immediately after the beginning of rubidium infusion. Mental stress is then performed using the subtraction paradigm described above, and the rubidium generator is started immediately after mental stress is completed. A 7.5-minute stress emission scan in list mode is started immediately after the beginning of rubidium infusion. Lastly, for approximately ½ the patients, pharmacologic stress with Regadenason 0.4 mg will be performed as well, followed by a 3rd 7.5 minute stress. Manual rigid-body registration of the CT and PET images is performed by using manufacturer-provided software.

**Static Reconstruction.** The diagnostic images will be reconstructed using ordered-subsets expectation maximization (OSEM) algorithm (4 iterations, 16 subsets) with a Gaussian post-

filter of 7 mm. A standard 2-minute delay will be applied to the list mode data for final attenuation correction static reconstruction.

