## Study Design and Methods

### Overall Study Design

This pilot-study (Figure 1) will recruit 24 patients from the Mental Stress Ischemia Mechanisms and Prognosis Study (MIPS), a longitudinal cohort study which enrolled 695 patients between July 2009 and July 2014 with a diagnosis of stable CAD from Emory University-affiliated hospitals or clinics. Each patient completed baseline myocardial SPECT imaging, as well as psychosocial, hemodynamic and microvascular assessments, and blood was obtained for inflammatory, neurohormonal, and immunological biomarkers prior, during and after mental stress and conventional (exercise or pharmacological) stress. These patients have been followed on regular intervals with in-person clinic visits every year and by telephone every 6 months.

The patients will be randomized 1:1 to HRV biofeedback intervention for 6 weeks or wait-list control. Each group will undergo a rest/stress Rb PET imaging protocol (detailed below) similar to regular clinical imaging except that stress will be performed with a standardized

arithmetic mental stress test rather than pharmacological stress. We will hold beta-blockers for 48 hours and calcium channel blockers and nitrates on the day of the testing. It is standard protocol to hold anti-ischemic medications, including beta-blockers, ace-inhibitors, calcium channel blockers and nitrates, before exercise stress imaging studies, and this is the protocol followed by other nuclear cardiology studies.

Figure 2: Protocol

[figure not shown]

The full protocol is detailed in Figure 2.

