### **Mental Stress Protocol**

Mental stress will consist of a 3-min math serial subtraction paradigm previously described by Soufer et al. The subjects will be asked to serially subtract 7 from number specified (i.e., 986) by the researcher; for patients who have difficulty with this task, easier serial subtraction will be provided for (e.g., by 4, 3, or 2). Throughout the task, to increase stressfulness and titrate difficulty, the patient will be prompted for faster performance and the starting number from which they were subtracting will be periodically changed (e.g., if the starting number was 986, it may be changed to 549 after performing a number of successful serial subtractions). Finally, to add an evaluation component, patients will be given negative feedback during the test. Blood pressure and heart rate will be recorded at 1-minute intervals. Subjective stress levels will be evaluated by the use of a visual analog scale; this will be repeated at the end of the stress test. At 60 seconds into the mental stress task, 30-60 mCi of Rubidium^82 (based on patient body weight) will be injected; images will be acquired as described below.

**Post mental stress testing:** Heart rate and blood pressure will be measured every minute for the first 5 minutes and at 5 minute intervals after the end of the mental test. Microvascular blood flow will also be continuously measured by PAT. Five minutes after the end of the test, 20 ml of blood will be drawn for catecholamine levels. Fifteen minutes after the mental stress test, arterial compliance measures will be repeated. Thirty minutes after the end of the test, brachial reactivity and simultaneous PAT reactive hyperemia will be repeated and the PAT device disconnected. Ninety minutes after stress, another 20 ml sample of blood will be drawn for future studies involving post-stress inflammatory measures, determined at a later date.

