**Endothelial function assessment:** Flow-mediated vasodilation (FMD) of the brachial artery: Brachial artery FMD using ultrasonography for determining endothelial function will be utilized before and 30 minutes after mental stress testing which has in previous studies been associated with peak reduction in endothelial function. We will determine endothelium-dependent FMD of the brachial arteries from two-dimensional ultrasound images according to established and validated methodologies. Images will be obtained with an Acuson 10 mHz linear array transducer and an Acuson Aspen ultrasound system. We will perform imaging with the subject resting supine for at least 10 minutes on a hospital bed in a quiet setting. For each subject, optimal brachial artery images will be obtained between 2 and 10 cm above the antecubital crease. After baseline measurements a blood pressure cuff is inflated to 60 mm Hg above systolic pressure over the proximal portion of the right arm for 5 minutes. Endothelium-dependent function will be determined during the first two minutes of release of the cuff as previous studies have shown that maximal dilatation occurs 1 minute after cuff deflation. Endothelium-independent responsiveness to nitroglycerin will not be measured so as to not affect the vascular measurements that follow. Four triggered events (defined as the end of the T wave on the EKG) for each intervention will be recorded and downloaded to an analysis system that

allows automatic edge detection of the M-line that defines the intima-media interface for both the near wall and the far wall of the artery using a customized software (Medical Imaging Applications Inc, Iowa). Analysis will be performed by individuals blinded to clinical and laboratory status of the subjects. A linear portion of the vessel will be chosen. Measurements from the twelve frames will be averaged for every intervention. The end point of measurement will be the percent change in diameter in response to reactive hyperemia.

Reproducibility of FMD measurements: The mean difference in FMD (%) between 2 consecutive assessments performed in 11 subjects an average of 8 days apart was 1.26 ( $\pm 0.76$ )%, with  $r=0.75$ . The mean difference in the FMD (%) between 2 readings of the same 11 measurements was 0.82 ( $\pm 0.48$ )%, with  $r=0.97$ .

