The augmentation index: The SphygmoCor is a computerized, portable and simple-to-use device used to assess pulse waveforms. Aortic pulse waveform, augmentation index, and central aortic pressure will be derived at the radial artery by applanation tonometry. Only high-quality recordings, defined as an in-device quality index  $>80\%$  (derived from an algorithm including average pulse height, pulse height variation, diastolic variation, and the maximum rate of rise of the peripheral waveform) and acceptable curves on visual inspection by the PI will be included in the analysis. Studies with inadequate tracings will be excluded. All pulse wave analyses will be taken in the sitting position in a quiet room after a brief period (at least 15 minutes) of rest. Augmentation index (Aix) and augmented pressure (AP) will be derived from this with the technique of pulse wave analysis. The merging point of the incident and the reflected wave (the inflection point) is identified on the generated aortic pressure waveform. AP is the maximum

systolic pressure minus pressure at the inflection point. The AIx is defined as the AP divided by pulse pressure and expressed as a percentage. Larger values of AIx indicate increased wave reflection from the periphery or earlier return of the reflected wave as a result of increased pulse wave velocity (attributable to increased arterial stiffness) and vice versa. In addition, because AIx is influenced by heart rate, an index normalized for heart rate of 75 bpm (AIx@75) will also be used in accordance with Wilkinson et al. Time to return of the reflected wave (Tr) is the time from the beginning of the derived aortic systolic pressure waveform to the inflection point and can be used as a substitute for pulse wave velocity (a higher pulse wave velocity will lead to a shorter Tr).

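### Regadenoson and a third scan for about half the patients contradict the stated two infusions, are missing from the expected-event lists, and have no visible time relative to the post-stress vascular measures

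*Protocol*

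**What the plan says.** The PET Imaging Protocol section states: "Two rubidium infusions of 1295 – 2220 MBq (35-60 mCi) are performed". It describes a rest scan and a mental stress scan, then adds that for roughly half the patients "pharmacologic stress with Regadenason 0.4 mg will be performed as well", with a third 7.5-minute acquisition. It mentions no third infusion, no rule for choosing the half, no visit and no clock time. The drug is simply last in the imaging sequence. Overall Study Design describes the stressor as a standardized "arithmetic mental stress test rather than pharmacological stress" and refers to Figure 2 for the full schedule; that figure is not available in the text.

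The Mental Stress Protocol section sets the later measures: "Fifteen minutes after the mental stress test, arterial compliance measures will be repeated", and "Thirty minutes after the end of the test, brachial reactivity and simultaneous PAT reactive hyperemia will be repeated". The section on endothelial function explains the 30-minute point as one "which has in previous studies been associated with peak reduction in endothelial function". It also leaves out the nitroglycerin test so that later vascular measures are not disturbed. FMD and arterial compliance are both named in secondary objective 4.

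Adverse event reporting lists the same five expected items twice, the second time as content of the consent form. PET radiation and the mental stress test are listed; regadenoson is not. The paragraph on minimizing risks does not mention it either.

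**The concern.** Staff following the PET section cannot tell from the count whether two or three infusions are authorised in the subset, and the design section suggests that no stress drug is used at all. The risk list meant for the consent form omits a stress drug that about half the patients will receive. The stopping rules are headed for mental stress testing only. They do not say whether a patient whose test was terminated may still be given the drug, in a trial that prefers patients with known mental stress ischemia.

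The order of events also matters for the data. If the drug is given in the same scanner session, it comes before post-stress compliance, FMD and PAT hyperemia. Any lingering effect would then be mixed with the effect of mental stress in those secondary measures, in one part of the sample only.

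**Working it through.** **Infusion count.** The PET section starts each 7.5-minute scan at the beginning of an infusion. Rest, mental stress and the added scan make three scans, so three infusions are implied in the subset against two stated. Assuming the third uses the same 35–60 mCi range, injected activity per session goes from 2 × 35–60 = 70–120 mCi to 3 × 35–60 = 105–180 mCi. This is injected activity, not radiation dose.

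**Number of patients.** Half of 24 is 12, or half of 30 is 15 if the recruitment ceiling in Participant selection is reached.

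**Timeline.** Time 0 is the end of the 3-minute task. The protocol gives two tracer times, so both are carried: 60 seconds into the task (Mental Stress Protocol), which is −2 min, and immediately after it (PET Imaging Protocol), which is 0. The drug is assumed to be given as soon as the mental stress scan ends. Any set-up time shortens the intervals to the later measures.

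| Step | Tracer at 60 s | Tracer after task |
|---|---|---|
| Mental stress scan ends, earliest drug | −2 + 7.5 = 5.5 | 0 + 7.5 = 7.5 |
| Third scan ends, at the earliest | 5.5 + 7.5 = 13 | 7.5 + 7.5 = 15 |
| Drug to compliance at 15 min | 15 − 5.5 = 9.5 | 15 − 7.5 = 7.5 |
| Drug to FMD/PAT at 30 min | 30 − 5.5 = 24.5 | 30 − 7.5 = 22.5 |
| Drug to 90-minute sample | 90 − 5.5 = 84.5 | 90 − 7.5 = 82.5 |

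**Other placements.** A drug given after the 15-minute compliance measure but before 30 minutes spares compliance and still precedes FMD/PAT. A drug given after FMD/PAT is complete reaches neither.

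**What is not exposed.** Mental-stress flow is acquired before the drug. The PAT ratio compares pulse amplitude during the task with rest. The post-stress catecholamine draw is at 5 minutes, before the earliest drug time of 5.5. None of these can be affected at that visit.

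**Carry-over.** The protocol gives no duration for the drug's effect, so only thresholds follow. An effect shorter than 7.5 minutes reaches no later measure. One of 9.5 to 22.5 minutes reaches compliance only, and one of 24.5 minutes or more also reaches FMD/PAT.

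**The case against.** The strongest reply is that the timing depends on a schedule not visible here. Being last orders the imaging steps and gives no clock time against the vascular measures, and Figure 2 may place the drug after them. This stands, so the timing is a conflict to resolve and not a demonstrated error. Same-session dosing is still the natural reading: one CT attenuation scan is described and no return to the scanner is mentioned.

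A reader might infer that the drug by itself breaks the rule that pulse wave analyses be "taken in the sitting position in a quiet room after a brief period (at least 15 minutes) of rest". The documents do not support that. Counted from the end of the last scan, patients without the drug also have only 15 − 7.5 = 7.5 to 15 − 5.5 = 9.5 minutes at the 15-minute point, with a blood draw at 5 minutes. The tension between the two sections exists for everyone.

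A reader might also infer that FMD is delayed. It need not be. A third scan ending at 13 to 15 minutes leaves 15 to 17 minutes before the 30-minute point, and imaging is to be done "with the subject resting supine for at least 10 minutes on a hospital bed in a quiet setting".

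On bias, a constant shift would cancel in the comparison of changes between arms if the drug were used equally across arms and visits. That is correct, but the visible text states no rule that secures it.

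On safety, radiation from the third scan falls under the generic PET item, a physician is present, and the consent pages are not shown. Only the drug itself is missing from the printed lists. The stopping rules' silence about a later drug is a gap worth closing, not a contradiction. Describing the drug as an add-on softens the conflict with Overall Study Design but does not repair the infusion count.

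**Conclusion.** Two parts hold on the visible text alone: the infusion count is wrong for the regadenoson subset, and both expected-event lists omit the drug. The timing part holds conditionally. If the drug directly follows the mental stress scan, about 12 of 24 patients receive it at most 7.5 to 9.5 minutes before compliance and 22.5 to 24.5 minutes before FMD/PAT, contrary to the protocol's own reason for omitting nitroglycerin. This assumes same-session dosing and the stated scan lengths. Whether any effect carries over, and how large it would be, cannot be judged from the documents.

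The point should be acted on for the safety text and the secondary vascular measures. It is no threat to the primary outcome.

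**What to change.** 1. In the PET Imaging Protocol, write *two rubidium infusions (three in the regadenoson subset)*, and note the exception in Overall Study Design.
2. Add regadenoson to both lists under Adverse event reporting, and check that the consent form names it.
3. State that it is not given to a patient who met an absolute termination criterion during mental stress.
4. State that regadenoson and the third scan follow the completed 30-minute FMD/PAT measures, with the same selection rule and the same visits in both arms. If that is not feasible, keep the subset balanced by arm and the same at both imaging visits, or drop the scan. Dropping it is simplest if the value has no planned use, since no stated objective names a pharmacologic flow measure.

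Items 1 to 3 cost only wording and a consent check. Item 4 means a return to the scanner and possibly a repeat CT attenuation scan, with its added exposure. Patients already stay for the 90-minute sample. If FMD/PAT takes 15 to 20 minutes, as before stress, it ends at 45 to 50 minutes, so that sample would follow the drug by about 90 − 50 = 40 to 90 − 45 = 45 minutes at most. The Mental Stress Protocol assigns that sample to future inflammatory work, although the Blood tests paragraph also lists it for catecholamines. Waiting until after it would protect it too, but is a costlier preference.

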### **PET Flow Analysis. *Modeling of Tracer Kinetics for Absolute Blood Flow.***

After reconstruction, images are translated into short axis orientation using our in-house software as per normal clinical protocol. Images are transferred to the Emory Cardiac Toolbox (ECTb) software that contains FlowTool for myocardial blood flow calculations. The calculation proceeds without further user interaction.

Thirty-two regions of interest (ROIs) are automatically drawn to characterize the uptake in different areas: 9 on the background, 4 concentric rings inside the left ventricle (LV), 2 inside the right ventricle (RV) and one each on the standard 17 segments. The rest and stress images are handled separately. This sampling procedure is performed on a late summed image (2-5 min) when the tissue to blood contrast is high. The ROIs are then transferred to each image to obtain the time activity curves (TACs). MBF is calculated from the TACs using the factor analysis method of El-Fakhri and the kinetic model of Hutchins. Briefly, the factor analysis is used to determine left and right ventricle and myocardial tissue factor curves. (Example results are shown in the above figure.) For each myocardial ROI, the determined contributions from LV and RV blood are subtracted. These spillover corrected curves and the LV factor curve are used as the inputs for kinetic modelling. It is recognized that the activity measured in the tissue ROIs is an underrepresentation of the true activity due to the finite resolution of the scanner and cardiac motion as discussed below.

The two-tissue compartment, three parameter model of Hutchins is fit to the data using a time-weighted least-squares figure of merit. The K1 parameter, which represents the rate that tracer moves from the blood to the first tissue compartment, is interpreted as representing flow times extraction (MBF\*mEF) where mEF is the myocardial extraction fraction of the tracer. Neither Rb nor NH3 are ideal flow tracers since their mEF is less than 1.0 and depends on flow. At a resting flow of 1 ml/min/g, mEF is approximately 0.5 for Rb; at 3.0 ml/min/g after pharmacological stress induction, it falls to approximately 0.3 respectively. mEF correction using Yoshida or Lortie equations is implemented in FlowTool as user selectable options. The user also has the option to apply a partial volume correction by applying a general recovery coefficient to the myocardial tissue.

MBF and derived MS-MFR are output on the current FlowTool display (Fig 1). Note that general implementation of versions of our FlowTool has been used in several clinical investigations. In

[figure not shown]

Figure 1. QC display of flow measurements showing stress and rest slices with superimposed sampling region (top left), corresponding RV/LV and myocardial TACS (right) and stress, rest and CFR polar maps with generic vascular territories.

addition, conventional measurements of LV function (EF, EDV, ESV, mass, thickening, dyssynchrony) will be performed as part of the ECTb processing.

**Blood tests:** Pre-, immediate-post mental stress, and 90 minute post mental stress blood samples will be centrifuged and the plasma stored for measurement of catecholamine levels. In addition samples will be stored for future measurement of markers of inflammation, oxidation and other biomarkers. The same protocols will be performed for all visits.

**Microvascular blood flow measurement using finger plethysmography:** We have employed a novel device that measures finger pulse wave amplitude responses using a robust modified form of volume plethysmography. Pulsatile arterial tonometry (PAT, Itamar-Medical, Israel) is designed to reflect only pulsatile arterial volume changes. The main features of this device include a proximal probe component and application of a constant counter pressure of 7 mm of mercury within the whole probe to keep venous transmural pressure deliberately negative. These features prevent venous pooling and stasis within the instrumented part of the finger and inhibit blood volume changes. The counter pressure serves to partially unload arterial wall tension, thus improving the range of the arterial pulse excursions. The probe components are connected via thin flexible tubing to isolated volume reservoirs to buffer pressure changes within the probe. A further volume reservoir not connected to the probe serves as a pressure reference. The pressure changes accompanying peripheral volume changes are fed to a personal computer by which the signal is bandpass filtered (0.3 to 30 Hz), amplified, displayed and stored. We will examine the mean PAT ratio, which reflects the magnitude of change in finger-tip blood flow induced by mental stress by measuring the ratio of pulse wave amplitude during mental stress compared to rest. The PAT ratio is expected to be lower during mental stress, consistent with stress-induced vasoconstriction. The assessment of pulse wave amplitude by peripheral arterial tonometry is relatively free of artifacts when individuals are monitored at rest and decreases in pulse wave amplitude are most likely due to microvascular constriction.

**Endothelial function assessment:** Flow-mediated vasodilation (FMD) of the brachial artery: Brachial artery FMD using ultrasonography for determining endothelial function will be utilized before and 30 minutes after mental stress testing which has in previous studies been associated with peak reduction in endothelial function. We will determine endothelium-dependent FMD of the brachial arteries from two-dimensional ultrasound images according to established and validated methodologies. Images will be obtained with an Acuson 10 mHz linear array transducer and an Acuson Aspen ultrasound system. We will perform imaging with the subject resting supine for at least 10 minutes on a hospital bed in a quiet setting. For each subject, optimal brachial artery images will be obtained between 2 and 10 cm above the antecubital crease. After baseline measurements a blood pressure cuff is inflated to 60 mm Hg above systolic pressure over the proximal portion of the right arm for 5 minutes. Endothelium-dependent function will be determined during the first two minutes of release of the cuff as previous studies have shown that maximal dilatation occurs 1 minute after cuff deflation. Endothelium-independent responsiveness to nitroglycerin will not be measured so as to not affect the vascular measurements that follow. Four triggered events (defined as the end of the T wave on the EKG) for each intervention will be recorded and downloaded to an analysis system that

allows automatic edge detection of the M-line that defines the intima-media interface for both the near wall and the far wall of the artery using a customized software (Medical Imaging Applications Inc, Iowa). Analysis will be performed by individuals blinded to clinical and laboratory status of the subjects. A linear portion of the vessel will be chosen. Measurements from the twelve frames will be averaged for every intervention. The end point of measurement will be the percent change in diameter in response to reactive hyperemia.

Reproducibility of FMD measurements: The mean difference in FMD (%) between 2 consecutive assessments performed in 11 subjects an average of 8 days apart was 1.26 ( $\pm 0.76$ )%, with  $r=0.75$ . The mean difference in the FMD (%) between 2 readings of the same 11 measurements was 0.82 ( $\pm 0.48$ )%, with  $r=0.97$ .

